### Procedures

#### Time Point: Enrollment (4 Weeks Before the Study to the Start of the Study)

An eligibility screen will be conducted and informed consent will be provided to those who are eligible. The following assessments will be carried out: the SDS (ie, the tool that is used for tracking changes in depressive symptoms over time during the course of a study and after treatment [35]) and physical examination findings (ie, height, weight, abdominal circumference, blood pressure, and heart rate). In addition, smoking status and exhaled carbon monoxide (CO) levels will be determined, and subject background data will be collected, including age; sex; medical history; comorbidities; presence or absence of allergies; subjective symptoms; drinking patterns, regarding subjects who drink daily or 3 to 4 times a week, and alcohol consumption, which is monitored and reported in converted values; sleep duration; smoking index (ie, the number of cigarettes smoked per day × years of tobacco use); nicotine dependence, measured by the Tobacco Dependence Screener and the FTND; and the subject’s first medication for smoking cessation.

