#### Secondary Outcomes

The secondary outcomes are as follows:

Successful smoking cessation rate. The percentage of subjects who stop smoking 12 weeks after aromatherapy (ie, the number of subjects who stop smoking divided by the total number of allocated subjects, as a percentage). Successful smoking cessation refers to a report of smoking cessation for the past 7 days and an exhaled CO level below 7 ppm [42].Changes in body weight, abdominal circumference, and glycolipid metabolism (ie, assessment of obesity following smoking cessation and dyslipidemia).Adverse events during the period of aromatherapy.Blood cell counts and biochemical tests by blood sample collection.Other laboratory findings or symptoms.Correlation between essential oil preference and smoker information items at first-time visit (ie, day of treatment start). Smoker information items include the following subject background data: age, sex, BMI, number of tobacco pieces consumed or smoked per day, FTND scores, and SDS and POMS scores. These items will be compared among different essential oil types.Changes in essential oil preferences over time.

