### Statistical Analysis

Research on the efficacy of aromatherapy as an adjuvant therapy for smoking cessation is scarce. Further, based on our research, the size of the effects of aromatherapy on psychological tests as measured by the SDS and the POMS in smokers has never been reported. Therefore, this study was designed as a pre-post single-arm clinical trial in which the sample size has been determined by considering the feasibility of registration. We will perform a comparison of the aromatherapy group with the standard treatment group from our previous study, “A Randomized, Multi-center, Double-Blind, Placebo-Controlled Trial for the Effects of Yokukansan on Depressive or Neurotic Smoking Patients during Smoking Cessation Therapy” (UMIN ID: 000027036). Similar to this aromatherapy study, the yokukansan study targeted the population of “depressed smoking patients.” For the yokukansan study, 100 patients were registered in our hospital.

Assuming that the registration number of this aromatherapy study would be comparable to that of the previous yokukansan study, this study planned to register 100 patients. The SDS scores and POMS subscale scores at baseline and at the 12-week time point will be compared using paired-samples *t* tests in the aromatherapy group of this study and in the standard treatment group of our previous study. Statistical significance was set at *P*<.05. Furthermore, concerning changes in data from baseline to the 12-week time point, a two-way analysis of variance will be used analyze the interaction between the standard treatment group and the aromatherapy group. The same will be used to compare changes in SDS and POMS scores before and after smoking cessation between the historical control group and the aromatherapy group of this study.

We will also compare the successful smoking cessation rates for a period of 12 weeks from the start of treatment between the standard treatment group and the aromatherapy group. Successful smoking cessation refers to a report of smoking cessation for the past 7 days and an exhaled CO level below 7 ppm. The successful smoking cessation rate was calculated by dividing the number of subjects who successfully stopped smoking 12 weeks after smoking cessation treatment by the total number of subjects who provided consent and received the treatment, multiplied by 100 to give the percentage. Descriptive statistics on subjects’ background data will be generated. No interim analysis will be performed.

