### Limitations

This study was designed to confirm the efficacy and safety of aromatherapy. The control group included patients in the usual care group of a previous study. This study was a pre-post single-arm study and not a double-blind randomized controlled trial. In addition, the aromatherapy survey was based on patient self-report, which may lead to inaccuracy in the frequency of inhaler use.

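### The comparison with the historical control names no covariate adjustment, so the estimated aromatherapy effect is open to confounding by characteristics this trial measures

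*Protocol article*

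**What the plan says.** The Limitations section gives the design: "This study was a pre-post single-arm study and not a double-blind randomized controlled trial". The control is the standard treatment group of the sponsor's earlier yokukansan trial, whose title calls it multi-center.

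The Statistical Analysis section fixes three things for the scores:

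- Within each group, SDS and POMS subscale scores at baseline and "at the 12-week time point will be compared using paired-samples" t tests.
- Between groups, for changes from baseline to week 12, "a two-way analysis of variance will be used analyze the interaction between the standard treatment group and the aromatherapy group". It then extends this to the mood scores of this trial's patients against the control: "The same will be used to compare changes in SDS and POMS scores before and after smoking cessation between the historical control group and the" (cut short here).
- "Statistical significance was set at" P<.05, with no statement of one or two sides.

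It also compares 12-week cessation rates between the two groups. No covariate, matching, weighting or stratification is named for any of these comparisons.

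The covariates exist on the aromatherapy side. The enrollment procedures list age, sex, smoking index, first cessation medication and "nicotine dependence, measured by the Tobacco Dependence Screener and the FTND". The Secondary Outcomes section lists "age, sex, BMI, number of tobacco pieces consumed or smoked per day, FTND scores, and SDS and POMS scores", to be compared among oil types. The only other stated use of background data is descriptive.

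**The concern.** In a randomised comparison, a two-factor analysis of group and time is defensible without covariates because allocation balances prognosis on average. Nothing does that here. The aromatherapy patients come from one hospital, were enrolled from July 2019 into the pandemic, agreed to aromatherapy, and exclude habitual users and people who cannot smell the oils. The controls come from an earlier trial with its own setting and selection. If the groups differ in dependence, age, sex or choice of patch or varenicline, and these predict change in mood or success in quitting, the difference is read as an aromatherapy effect.

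The Objective is to judge whether a phase III trial is reasonable, and the Conclusions tie a positive result to possible use. The historical comparison is the only part of the plan that can separate aromatherapy from the ordinary course of mood during cessation. An avoidable weakness there therefore matters.

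**Working it through.** **Inputs.** From the article: "this study planned to register 100 patients" (76 recruited by May 2022); 220 per group in the earlier trial, of whose patients 100 were registered at this hospital; P<.05. The article does not say whether all controls or only same-hospital controls are used. It gives no SD, correlation or effect size, and the target of 100 rests on feasibility, so there is no power figure to reproduce. Assumed below: two-sided test, SDS SD 7 to 9, baseline to week-12 correlation ρ of 0.3 to 0.7, and about 50 same-hospital controls if the 100 were split equally.

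**1. What the interaction estimates.** With two time points it is

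(mean change, aromatherapy) − (mean change, control).

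If a covariate shifts change by γ per unit and its group means differ by δ, this quantity takes in γ × δ whatever aromatherapy does. A two-factor model has no term to remove it.

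**2. What a bias b does to the error rate.** SE = SD of change × √(1/n1 + 1/n2). The two-sided error is Φ(−1.96 + b/SE) + Φ(−1.96 − b/SE). With an assumed SD of change of 8:

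- 100 against 220: SE = 8 × 0.1206 = 0.965
- 100 against 50: SE = 8 × 0.1732 = 1.386

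| Bias b (SDS points) | 100 vs 220 | 100 vs 50 |
|---|---|---|
| 0.5 | 8.1% | 6.5% |
| 1 | 17.9% | 11% |
| 2 | 54.5% | 30% |

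**3. A route to imbalance in the article itself.** Study Design says both studies took SDS 39 to 59. The Exclusion Criteria remove scores of 53 or higher, although that line can also be read as tied to psychiatric medication. Suppose the aromatherapy group is 39 to 52 and the control 39 to 59, from one population with mean μ and with no treatment effect. Expected change is −(1 − ρ)(mean baseline − μ), so the spurious difference is (1 − ρ) × (control baseline mean − aromatherapy baseline mean).

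- μ 38, SD 7, ρ 0.7: 0.3 × (43.87 − 43.44) = 0.13
- μ 46, SD 9, ρ 0.5: 0.5 × (47.88 − 45.59) = 1.14

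So 0.1 to 1.1 points, here against aromatherapy. ANCOVA on baseline has a bias of about 0 in this case.

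**4. Whether baseline-adjusted ANCOVA is always better.** If the source means are μ1 (aromatherapy) and μ2 (control), with the same ρ:

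- change-score bias = (1 − ρ) × [(μ1 − μ2) − (difference in baseline means)]
- ANCOVA bias = (1 − ρ) × (μ1 − μ2)

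With SD 8 and ρ 0.6:

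| Case | Change score | ANCOVA |
|---|---|---|
| Means 42 and 42; ranges 39–52 and 39–59 | 0.4 × [0 − (44.70 − 45.98)] = 0.51 | 0 |
| Means 40 and 42; range 39–59 in both | 0.4 × [−2 − (45.24 − 45.98)] = −0.50 | 0.4 × (−2) = −0.80 |

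In the second case both analyses flatter aromatherapy, and ANCOVA does so more. Neither dominates when the source populations may differ.

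**5. Pairing.** Without selection on baseline, ignoring the pairing inflates the SE of the interaction by 1/√(1 − ρ): 1.20, 1.41 and 1.83 at ρ = 0.3, 0.5 and 0.7. The true error falls to 1.9%, 0.6% and 0.03%. An effect with 80% power when paired has 68%, 51% and 22%. With baseline restricted to 39–59 (SD 8, ρ 0.6, mean 42, 100 against 220), the SE is 1.04 against 0.81 paired, and the true error is about 1.1%. The point estimate is the same either way with complete data. A repeated-measures form holds the error near 5%.

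**The case against.** **The standard errors may be right.** A reader might infer that they are wrong because the ANOVA will treat each patient's two scores as independent. The article does not say so. It pairs the within-group tests and applies the ANOVA to change from baseline, which is naturally read as repeated measures, and an article may leave the model form to a fuller plan. Only the ambiguity stands. If the ordinary form were used, the error would be conservative and would not bias the estimate.

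**Bias is not shown.** A reader might also infer that the estimates are biased. Study Design states one SDS range for both studies, the control subset is not specified, and no control data are given. Open to bias is as far as the documents go. Nor are baseline SDS and POMS ignored: they are the first time point of the analysis.

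**ANCOVA is not the correct replacement by right.** A reader might infer that conditioning on baseline removes differential regression to the mean. Step 4 shows that this needs a common source population, which a historical control does not guarantee.

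**The aims are modest.** The abstract concedes that this is not a rigorous validation and that the methods were not set with full rigor. Covariate lists often sit in an analysis plan. This lowers the urgency but does not remove the point: the article positively names a two-factor method, and its caveats mention neither confounding nor adjustment.

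**Conclusion.** The point holds in this form. A non-randomised historical comparison is fixed with no covariate adjustment, while prognostic covariates are collected and given other uses. The estimated effects on SDS, POMS and cessation are therefore open to confounding by measured case mix, of unknown size and direction.

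The error rates of 8%, 18% and 54% for biases of 0.5, 1 and 2 SDS points show scale only. They rest on an assumed SD of change of 8 and 100 against 220 patients, and they are lower with fewer controls. The 0.1 to 1.1 points from entry ranges apply only if the ranges really differ and both groups come from one population. Standard errors that are too wide are a risk only if the repeated-measures form is not used. Adjustment is an addition that makes the comparison more credible; it does not turn it into a randomised one.

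**What to change.** 1. Name the ANOVA as repeated-measures, with patient as a random or within-subject factor.
2. Add a prespecified adjusted comparison: ANCOVA, or a mixed model with a patient effect, of the follow-up SDS and POMS scores on group, baseline score, age, sex, FTND, cigarettes per day and first cessation drug. For the cessation rate, use logistic regression or standardisation on the same covariates.
3. Report adjusted and unadjusted results side by side, with a baseline table of both groups.
4. State that adjustment removes only measured confounding, and that change-score and ANCOVA results may differ if the source populations differ.
5. Reconcile the SDS range in Study Design and the Inclusion Criteria with the line on 53 or higher in the Exclusion Criteria, and state the range that applied in each study.

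The cost is analysis wording and extraction from the sponsor's own earlier trial. The article does not confirm that that trial recorded the same covariates, so this must be checked first and the list cut to what both studies hold. A few patients may have missing covariates, and the plan should say how they are handled.

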### Protection of Personal Information

All parties involved in this research shall strictly protect the personal information of the subjects in accordance with the Personal Information Protection Law. Personal information will be used to identify subjects so that accurate data can be obtained for each subject, and the personal information obtained will be managed appropriately. When information obtained from the research is published by the principal investigator or others, sufficient care will be taken to ensure that subjects are not identified.

### Early Discontinuation of the Study

The Data and Safety Monitoring Committee will recommend discontinuation of the study to the principal investigator if the experimental treatment is deemed unsafe based on safety information, including reports of serious adverse events and information outside of the study. If the committee reports to the principal investigator that the study needs to be discontinued due to safety issues or for other reasons, the principal investigator will deliberate the report and will promptly inform the secretariat in writing about the results of the deliberation. In addition to the head of the institution where the study is conducted and the IRB, the subjects will also be informed.

### Ethics Approval

This study was approved by the Kyoto Medical Center IRB on June 17, 2019 (approval No. 19-016) and has been registered in the UMIN Clinical Trials Registry (UMIN000043102).

## Results

Enrollment started on July 1, 2019. As of May 2022, 76 patients have been recruited. In the original plan, recruitment should have been finished on June 30, 2021. However, the number of subjects decreased due to the COVID-19 pandemic, and the study inclusion period was extended by 1 year (ie, until the end of June 2022) with the approval of the IRB on May 17, 2021. The observation period (ie, follow-up) will last 3 months after the enrollment of the last subject, and the study period will last for 3 years and 3 months (July 2019 to September 2022). The corresponding author will have complete access to the study data and will submit the report for publication. The results of this research will be published in international peer-reviewed journals. Both positive and negative results will be reported. In addition, the study results will be shared on the UMIN Clinical Trials Registry. Our findings will be posted on the hospital website and will be made publicly available.

## Discussion

### Principal Findings

This study is the first clinical trial study to examine the psychological effects of aromatherapy on smokers with depression. Hence, we believe that this study is of major significance. If aromatherapy can inhibit an increase in a transient propensity for depression, it can be expected to increase the rate of successful smoking cessation, which will not only reduce the risk of NCDs, but will also lead to a reduction in future medical expenses. Moreover, as aromatherapy has been reported to reduce insomnia [19], alleviate fatigue [20,21], and improve cognitive function [23], we believe that smoking cessation may have the secondary benefit of alleviating the adverse effects of smoking, such as insomnia [43,44], fatigue [45], and reduced ability to focus [44].

### Limitations

This study was designed to confirm the efficacy and safety of aromatherapy. The control group included patients in the usual care group of a previous study. This study was a pre-post single-arm study and not a double-blind randomized controlled trial. In addition, the aromatherapy survey was based on patient self-report, which may lead to inaccuracy in the frequency of inhaler use.

### Comparison With Previous Work

Smoking can cause or exacerbate negative emotions [5] and increase the risk of developing depression [6,7]. Furthermore, it has been reported that when patients with mental disorders are unstable and quit smoking, their depressive symptoms become temporarily exacerbated [8]. We have previously reported that depressive tendencies are common among smokers without a history of mental disorders [46] and that depressive tendency is the most significant factor that prevents successful smoking cessation [47]. Although aromatherapy showed potential therapeutic efficacy against depression [18], research on the efficacy of aromatherapy as an adjuvant therapy for smoking cessation is scarce. Therefore, it is significant to examine the psychological effects of aromatherapy on smokers with depression in this study.

### Conclusions

This is a pre-post single-arm study. In this study, the group treated with aromatherapy will be compared with the group that received standard treatment in a previous randomized controlled trial as the control group. If this study shows that aromatherapy has psychological benefits for patients with depression who are undergoing smoking cessation treatment, then aromatherapy could be used to improve the success rate of smoking cessation, thus reducing the risk of NCDs and lowering future medical care needs. A phase III trial is intended to be conducted to confirm the findings and correct the limitations of this study.

## Abbreviations

CO: carbon monoxide
CTCAE: Common Terminology Criteria for Adverse Events
FTND: Fagerström Test for Nicotine Dependence
IRB: Institutional Review Board
NCD: noncommunicable disease
POMS: Profile of Mood States
SDS: Zung Self-Rating Depression Scale
UMIN: University Hospital Medical Information Network
